## Abstract

**Background:**

According to the projections of the World Health Organization, 15% of all disabilities will be associated with mental illnesses by 2020. One of the mental disorders with the largest social impacts due to high personal and family costs is psychosis. Among the most effective psychological approaches to treat schizophrenia and other psychotic disorders at the world level is cognitive behavioral therapy. Recently, cognitive behavioral therapy has introduced several tools and strategies that promote psychological processes based on acceptance and mindfulness. A large number of studies support the effectiveness of mindfulness in dealing with various mental health problems, including psychosis. This study is aimed at determining the efficiency of a mindfulness-based program in increasing cognitive function and psychological well-being in patients with a first episode of schizophrenia and a high risk mental state (those at risk of developing an episode of psychosis).

**Methods and design:**

This is an experimentally designed, multi-center randomized controlled trial, with a 3-month follow-up period. The study participants will be 48 patients diagnosed with schizophrenia (first episode) and 48 with a high-risk mental state, from Santiago, Chile, aged between 15 and 35 years. Participants will be submitted to a mindfulness-based intervention (MBI), which will involve taking part in eight mindfulness workshops adapted for people with psychosis. Workshops will last approximately 1.5 hours and take place once a week, over 8 weeks. The primary outcome will be the cognitive function through Measurement and Treatment Research to Improve Cognition in Schizophrenia (MATRICS) and the secondary outcome will be psychological well-being measured by self-reporting questionnaires.

**Discussion:**

The outcomes of this trial will add empirical evidence to the benefits and feasibility of MBIs for the psychotherapeutic treatment of patients with schizophrenia and high-risk mental states in reducing cognitive impairment in attention, working memory, and social cognition, as well as increasing the psychological well-being by empowering the patients’ personal resources in the management of their own symptoms and psychotic experiences.

**Trial registration:**

ISRCTN registration number ISRCTN24327446. Registered on 12 September 2016.

**Electronic supplementary material:**

The online version of this article (doi:10.1186/s13063-017-1967-7) contains supplementary material, which is available to authorized users.

## Background

According to projections of the World Health Organization, 15% of all human disabilities will be associated with mental illnesses by 2020 [1]. One of the mental disorders with the largest social impacts due to high personal and family costs is psychosis, particularly schizophrenia [2]. At present, national and international clinical guidelines suggest favoring an intervention approach that aims to minimize the time an individual is without treatment and to continue treatment during all the phases of the illness. This has led several countries to modify their public policies towards an early intervention of the disorder. Evidence suggests a better prognosis for patients with a lower duration of untreated psychosis [3, 4].

Early intervention not only focuses on the first psychotic episode but also in premorbid states, characterized by subclinical signs and symptoms and with specific features, including delusional beliefs, attenuated hallucinations, and disorganized speech with intact reality testing but of sufficient severity and/or frequency that it is not discounted or ignored. Additionally, symptoms should have worsened in the past year with sufficient clinical discomfort for the affected patients or their relatives to pursue specialized help. Such attenuated symptoms have been characterized as a high-risk mental state for psychosis, collected by DSM-5 to be studied as an Attenuated Psychosis Symptom Syndrome [5]. While not all individuals who experience a high-risk mental state derive into a psychosis, all those with schizophrenia showed a high-risk premorbid state. Therefore, it is extremely relevant to determine the factors that effectively predict a transition towards psychosis [6].

Several countries, including the United Kingdom, Australia, or Canada, to name a few, have included early intervention as a core approach to address schizophrenia. In Chile, its treatment has been a public policy priority. As a matter of fact, first-episode schizophrenia is the first mental health condition included in the Explicit Health Care Guarantees. Clinical guidelines suggest an integral approach, i.e., one that considers the psychosocial and pharmacological dimensions. Among the psychosocial interventions with the best results in addressing schizophrenia and other psychotic disorders at the world level is cognitive behavioral therapy. Recently, cognitive behavioral therapy has introduced several tools and strategies that promote psychological processes based on acceptance and mindfulness [7].

### Mindfulness-based interventions (MBIs)

Mindfulness is a research area in psychology that has experienced the greatest development in recent years. These interventions include acceptance and commitment therapy (ACT), mindfulness-based cognitive therapy, mindfulness-based stress reduction therapy, or dialectical behavior therapy. This set of procedures shares the basic notion that, in order to achieve adequate psychological functioning, individuals should change the way in which they relate to their symptoms instead of eliminating them [8]. Recently, these interventions have been grouped under the label of third wave cognitive behavioral therapies [9]. ACT and MBIs are among the third wave therapies used efficiently in psychosis.

Mindfulness can be understood as a specific form of meditation that seeks to increase different psychological functions by means of a synergic effort between attention regulation, self-awareness and emotional regulation, thereby increasing psychological resilience and self-regulation [10]. Mindfulness has been defined as, “*Paying attention in a particular way: on purpose, in the present moment, and non-judgmentally*” [11]. It has also been conceptualized as a theoretical construction, as a practice and as a psychological process [12]. Training in mindfulness from a Western and academic standpoint has been developed and disseminated through standardized group programs lasting from 8 to 10 weeks and in clinical and health contexts [8, 13].

Such approaches rely on broad empirical support. In fact, recent meta-analyses suggest that mindfulness is an effective intervention for the treatment of several mental health disorders, including depression and anxiety [14, 15]. However, one recent meta-analysis revealed that ACTs and MBIs show promising results in the management of positive and negative symptoms of psychosis [16].

Specifically, the first study of mindfulness in psychosis was conducted in the United Kingdom with patients who suffered stress-induced hallucinations. Patients attended to six mindfulness sessions. The outcomes of this non-controlled study revealed an increase of mindfulness skills in the management of stress-causing thoughts and images. Additionally, the perception regarding the psychological well-being of patients had improved [17]. On the other hand, Chadwick et al. [17] suggested a series of changes to the MBIs when used in psychotic patients in order to ensure the procedure’s feasibility in this population group. Subsequently, Chadwick et al. [18] performed the first controlled study assessing mindfulness skills and overall patient functioning. Both measures improved in the expected direction and showed significant outcomes in intra-group comparisons, but did not do better than the control group. The second controlled clinical trial was conducted in Spain with a small sample of psychotic patients [19], and revealed that, when patients increased their acceptance rates, they also had a less stressing relationship with their thoughts and emotions, in addition to improvements in overall functioning; however, only the first outcome was statistically significant compared to the control group. Another more solid study in terms of the number of participants (N = 98) and the introduction of follow-up measures (18 months) was performed by Lee and Chien [20]. The outcomes of their study revealed that patients showed improved levels of illness insights and overall functioning, and a reduction in symptom severity and in the number and length of hospitalizations. All of these indicators were statistically significant compared to the control group (usual treatment). Recent studies have confirmed the results mentioned above [21, 22]. Other non-controlled studies have proven the feasibility of using mindfulness in patients with psychosis [23–25].

On the other hand, several qualitative studies have revealed that practicing mindfulness results in a less stressful relationship between patients and their symptoms, with greater flexibility and control over them. This change has a direct impact on the way in which a person relates both to others and to themselves, increasing their confidence and the sense of self-agency. In other words, a person gains an active role in the way they face their symptoms and life, strengthening a self-image that is not only centered around the absence or presence of psychotic symptoms but on their personal resources as the main focus of recovery [26–28].

Considering all the research in this area, i.e., more than 20 studies including randomized, non-controlled, qualitative, and single case clinical trials [29], two aspects can be pinpointed concerning the use of mindfulness in psychosis. Firstly, that mindfulness reduces the stress associated to psychotic symptoms and thereby promotes patient recovery and, secondly, its implementation in clinical centers is both safe and viable.

### The relevance of the mindfulness study in cognitive functions and psychological well-being

#### Mindfulness and cognitive functions

Cognitive impairments have been described as a core element of schizophrenia; indeed, 90% of patients have difficulties in this area [30, 31]. What is relevant is that these impairments are found before the onset of schizophrenia, which suggests that they are not a consequence of the illness but rather a vulnerability factor for schizophrenia [32] and a functionality predictor in patients [33]. Cognitive functions subject to the greatest decline in the transition from a high-risk mental state to a first psychotic episode are working memory [34], attention [35], and social cognition [36]. For instance, working memory has been defined as the most solid indicator in the transition between a high-risk mental state and schizophrenia. On the other hand, improvements in attention could be a remission indicator in high-risk people with schizophrenia [35], while the reduction of social cognition skills have been related to the length and severity of symptoms [37].

The control of attention in mindfulness is one of the pillars to achieve improved psychological flexibility and therefore greater response options facing adverse stimuli. In fact, expert meditators score higher in attention tests than non-meditators or beginners [38]. On the other hand, working memory has been related to other cognitive domains that are impaired in schizophrenia, such as attention and planning [39], and other executive functions, including inhibitory control and mental flexibility [40]. As background information, while mindfulness has a major impact on working memory [41, 42], this impact depends on the time devoted to meditation, being greater in people who meditate regularly compared to beginners [42, 43]. Similarly, working memory has been related to social cognition [44]. For instance, the cognitive training of working memory improves social perception in patients with schizophrenia [45].

#### Mindfulness and its impact on psychological well-being

Psychological well-being is a key area in the current conception of health [1]. In other words, it is not only the absence or reduction of symptoms that matters in the treatment of severe mental disorders such as schizophrenia [46]. The concept of mental health recovery notes that people should lead a purposeful and meaningful life, regardless of whether they have a mental disorder. However, a review study concluded that only a very small amount of interventions have proven effective in improving the psychological well-being of patients with schizophrenia [47]. Numerous studies, however, emphasize the favorable impacts of mindfulness, among them a reduction of symptoms and, above all, the development of a more favorable way of relating to own experience, with greater presence and acceptance, thereby promoting the sense of self-empowerment and improving a broader self-image not exclusively focused on the presence or absence of symptoms [21, 28]. In this sense, focusing attention on own feelings and managing them is related to improved emotional intelligence, also a very important aspect in the social sphere [48, 49]. An increase in the aspects mentioned above is among the main findings of qualitative research concerning mindfulness in psychosis [31]. It should be noted that this project understands psychological well-being from two perspectives. The first refers to a positive dimension which aims at increasing positive emotions and more flexible psychological states (mindfulness), while the second refers to a symptomatic sphere where a less aversive relationship with private events is expected and thus a reduction in psychological discomfort [46].

The purpose of this study is to determine how efficient MBIs can be in increasing cognitive functions and psychological well-being in patients with a first episode of schizophrenia and patients in a high-risk mental state, and thus define the scope of mindfulness to increase these areas of functioning. The specific goals are to (1) determine how efficient a mindfulness intervention can be in increasing attention, working memory, and social cognition rates, compared with the control group; (2) establish which spheres of psychological well-being increase (positive dimension) and which decrease (symptomatic dimension) with mindfulness training, compared to the control group; (3) determine whether the expected outcomes (increased cognitive functions and psychological well-being) are still present 3 months after the intervention has finalized, and additionally establish whether impacts are greater in participants who continue practicing mindfulness compared to those who fail to continue the practice; and (4) describe, on the one side, the subjective experience of patients regarding the feasibility of implementing such an intervention in a local context and, on the other, the benefits of mindfulness for patients compared to other psychosocial interventions in the context of mental health public policies in Chile.

The hypotheses are as follows. (1) MBIs will increase executive functions. Specifically, a statistically significant increase is expected in attention, working memory, and social cognition rates compared to the control group. (2) Subjective psychological well-being rates will increase significantly in the mindfulness group compared to the control group. (3) The outcomes in the areas described will persist 3 months after; however, impacts will be greater on people who continue practicing mindfulness compared to those who do not.

The questions that guide the qualitative goals are as follows. (1) What were the benefits and shortcomings found during the workshop? (2) Do patients continue with this practice and mainstream the outcomes into other areas of their lives? (3) What differences and similarities are perceived by patients between mindfulness and traditional psychosocial interventions?

## Methods and design

This is a multi-center randomized controlled trial (RCT) with two parallel arms and 1:1 allocation. A mixed analysis approach will be used. To assess the RCT’s effectiveness, a quantitative method will be used, while a qualitative approach will help understand subjective change processes considering cultural traits.

### Participants

Patients will be recruited from six clinical centers from three different cities in Chile; four in Santiago, one in Valdivia, and one in Osorno. Ninety six people are expected to take part in the study, of which 48 will be patients diagnosed with a first episode of schizophrenia (divided into 24 trial and 24 controls) based on the following criteria: patients with a psychotic episode without a prior diagnostic of schizophrenia, patients diagnosed with schizophrenia for the first time, and/or patients who persist with the schizophrenia diagnosis after the first episode. Additionally considered is the participation of 48 patients under a high-risk mental state (divided into 24 trial and 24 controls) who meet the criteria of an Attenuated Psychosis Symptom Syndrome, including delusional beliefs, attenuated hallucinations, and disorganized speech with intact reality testing but of sufficient severity and/or frequency that it is not discounted or ignored [5]. Sample size was estimated considering a previous RCT for people with schizophrenia on both the MBI [20] and a cognitive remediation program [50]. The sample size was calculated by using the statistical program G*Power [51]. The sample required to detect statistically significant differences in the cognitive functioning for a two-tailed test of the proportions with an effect size of 0.80, an alpha of 0.05, and a power of 0.90 is 2 × 39. With an estimated 15–20% drop-out over 3 months, we decided to include 96 persons in the trial, 48 allocated in each intervention arm. The inclusion criteria are (1) patients diagnosed with a first episode of schizophrenia or in high-risk of psychosis, as applicable; (2) aged between 15 and 35 years; and (3) clinical stability defined by medical and psychometric criteria (e.g., PAANS). Exclusion criteria are (1) risk of suicide; (2) severe intellectual disability (mental retardation); (3) medical illness inconsistent with the intervention; and (4) substance abuse or dependence in the past 6 months. Figures 1 and 2 summarize the process of randomization, group allocation, and assessment. The SPIRIT checklist is available in Additional file 1.

**Fig. 1 Fig1:**
[figure not shown]
This figure illustrates the process of randomization, allocation assessment, and follow-up throughout the study

**Fig. 2 Fig2:**
[figure not shown]
Schedule of enrollment, intervention, and assessments for the mindfulness-based intervention

### Procedure

Participants, as defined above, will be randomly allocated (a simple randomized sampling will be used) to the trial or control group. Randomization to either trial or treatment as usual will be conducted by independent researchers using a stratified block randomization procedure with a computer-generated allocation sequence. Health experts who will implement the MBIs will be blind to this procedure and will not carry out the assessment.

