#### Intervention group

Participants will be provided with the MBI, plus treatment as usual, divided into 24 patients diagnosed with a first episode of schizophrenia and 24 patients in a high-risk mental state (groups do not include both profiles). This means that both groups will be submitted to eight sessions of mindfulness workshops adapted for patients with psychosis [17]. The proposed duration for each session is 1 hour and a half, once a week. The intervention will take place in the facilities of each participating clinical center and led by a mindfulness coach with specific training in the target audience. The main project researcher will supervise and train each coach in the application of mindfulness in psychosis. The workshop includes take-home exercises. Additionally, every participant will get a pen drive or CD with guided mindfulness practice audios and a booklet with the contents of each session. Groups will be composed of up to eight members and two workshops have been planned by every participating institution.

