### Data analysis

A mixed qualitative and quantitative analysis method will be used. Qualitative information will be collected by means of semi-structured interviews and assessed with the Grounded Theory. This data analysis approach is widely used in social sciences and was previously applied for the analysis of the subjective experience of patients with psychosis [26]. This methodology will analyze the patients’ subjective experience regarding the feasibility and contribution of this type of intervention in a local context. At the quantitative level, the hypothesis will be contrasted though a mixed designed ANOVA in order to consider both the impacts of the intervention (inter subjects) and time (intra-subject; pre, post, and follow-up measurements) in every variable assessed. The analysis will help prove the hypotheses regarding the efficiency of this intervention in both patient groups. If statistically significant differences are found between the trial and control groups at the beginning of the intervention, corrections will be conducted using an ANCOVA.

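### The Procedure section gives two incompatible allocation methods, and only stratified blocking fits the planned 24/24 split per diagnosis; the strata should be named and carried into the arm comparisons

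*Protocol article*

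**What the plan says.** All references are to the protocol article.

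- **Procedure**, first sentence, on the random allocation of participants: "a simple randomized sampling will be used) to the trial or control group".
- **Procedure**, next sentence: independent researchers randomise, "using a stratified block randomization procedure with a computer-generated allocation sequence". The section names neither the strata nor the block size.
- **Methods and design**: the trial is set up "with two parallel arms and 1:1 allocation".
- **Participants**: "48 will be patients diagnosed with a first episode of schizophrenia (divided into 24 trial and 24 controls"), and likewise "48 patients under a high-risk mental state (divided into 24 trial and 24 controls").
- **Intervention group**: the arm is "divided into 24 patients diagnosed with a first episode of schizophrenia and 24 patients in a high-risk mental state (groups do not include both profiles"), so the split by diagnosis is repeated and workshops hold one diagnosis only.
- **Data analysis**: a mixed-design ANOVA is to consider "both the impacts of the intervention (inter subjects) and time". The only adjustment named is an ANCOVA if the arms differ significantly at baseline. The section also says that the analysis addresses efficacy in both patient groups, but it does not name diagnosis as a factor.

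**The concern.** Simple randomisation places no restriction on arm sizes, whereas stratified blocking fixes them within each stratum as blocks complete. The two sentences concern the same step. The word sampling does not rescue the first, because the parenthesis qualifies allocation to the arms and not selection of patients. This is therefore a contradiction in what is stated and not a detail left to a fuller document.

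Two things depend on it. First, a reader cannot tell how patients were allocated, and the planned numbers by diagnosis are credible under only one of the two methods. Second, the analysis should follow the design: a factor used to restrict the randomisation belongs in the arm comparison, and the model as written has only arm and time.

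**Working it through.** **1. The plan's own numbers.** Two diagnoses × two arms × 24 = 96 in total, with 48 per arm and 48 per diagnosis. These agree across the Methods and design, Participants and Intervention group sections.

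**2. Simple 1:1 allocation.** Let X be the number allocated to the intervention among the 48 patients of one diagnosis, X ~ Binomial(48, 0.5).

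- P(X = 24) = C(48,24)/2^48 = 0.1146, or 11.5%.
- Both diagnoses at 24/24: 0.1146² = 0.0131, or 1.3%.
- P(X ≤ 20 or X ≥ 28) = 0.312, or 31% per diagnosis.
- In at least one diagnosis: 1 − (1 − 0.312)² = 0.527, or 53%.
- Central 95% range of X: 17 to 31.

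**3. Blocks stratified by diagnosis.** With all blocks complete, 24/24 in each diagnosis is certain.

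**4. What an unequal split costs.** Take the effect size of 0.80 and two-sided alpha of 0.05 from the Participants section, within one diagnosis. By the normal approximation, power = Φ(0.80 × √(n₁n₂/(n₁+n₂)) − 1.96).

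- 24/24: 0.80 × √12 = 2.771; Φ(0.811) = 0.791.
- 20/28: 0.80 × √(560/48) = 2.733; Φ(0.773) = 0.780.

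The loss is about one percentage point.

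**5. Leaving diagnosis out after balancing on it.** Let the diagnoses differ by D within-diagnosis SDs on the outcome. The document gives no value, so D = 0.5 to 1.0 is an assumption. With equal numbers per diagnosis, omitting the factor multiplies the residual variance by 1 + D²/4. The true variance of the arm difference does not change, because diagnosis is balanced. The real type I error of a nominal 5% between-subject test is then 2 × (1 − Φ(1.96 × √(1 + D²/4))).

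| D (assumed) | Variance ratio | True type I error |
|---|---|---|
| 0.5 | 1.0625 | 4.3% |
| 1.0 | 1.25 | 2.8% |

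Cross-check: D = 1.0 means that diagnosis explains 0.25/1.25 = 20% of the variance. A simulation of 24/24 per diagnosis at that value gave a type I error of 2.8% without the diagnosis term and 4.9% with it. At an illustrative effect of 0.6 SD, power was 86% without the term and 90% with it.

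**6. The arm-by-time test.** This test works on within-person changes. A diagnosis gap that is the same at every visit subtracts out of each change, so it enters neither the effect nor its error. A simulation with three visits and an assumed within-person correlation of 0.7 agrees: for gaps of 0.5 and 1.0 SD the type I error was 5.2% in both cases. The arm main effect averaged over visits was conservative, at 4.1% and 2.3%.

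**The case against.** **The second sentence is the operative one.** It is detailed, and it gives the task to independent researchers, so the parenthesis may be only loose wording. A reader might infer that the clinical centres could apply the wrong scheme. The text does not support that, since the centres are not said to do the allocating. The contradiction itself remains.

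**24/24 is a plan, not a requirement.** The Participants section speaks of the people expected to take part. A reader might conclude that simple randomisation makes the design unworkable. It does not: it can produce 24/24 but cannot guarantee it, and a moderate imbalance costs very little power.

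**The model leg is weaker than the allocation leg.** The strata are never named, the reference to both patient groups could mean separate analyses by diagnosis (which would deal with that factor), and an analysis plan that is not shown may add terms. A reader might also infer inflated false positives, or damage to the hypothesised effect on change. Neither follows: the error is in the conservative direction, and it touches only a between-subject comparison when the gap is stable. What stands is that the model as written omits the one grouping by which the planned numbers are split.

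**Centre as a stratum.** A reader might want stratification by centre as well. The document does not say that this is done. Six centres × two diagnoses gives 12 strata of about 8 patients if recruitment were even, and the document gives no enrolment by centre. With blocks of 4 and 6 (assumed), a simulation reached exactly 24/24 in about 31% of runs per diagnosis and about 10% for both, because blocks stay incomplete. Adding centre is therefore not a way to secure the planned split.

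**Conclusion.** The point holds. The Procedure section states two incompatible allocation methods, and the planned numbers fit only the restricted one: under simple allocation both diagnoses reach 24/24 about 1.3% of the time. These probabilities need no assumption beyond independent 1:1 allocation of 48 patients per diagnosis.

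The statistical damage is modest: about one point of power for a 20/28 split and, for a between-subject arm test without diagnosis, a true type I error of about 4.3% to 2.8% under an assumed gap of 0.5 to 1.0 SD. The arm-by-time test is not affected if the gap is constant over time. The document does not support reading this as a threat to validity or as inflated type I error. It is a contradiction to be corrected, with a small gain in precision from aligning the model with the allocation.

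**What to change.** 1. In the Procedure section, delete the parenthesis on simple randomised sampling. State blocked randomisation stratified at least by diagnosis (first episode / high risk). Name centre as a stratum only if the existing sequence uses it.
2. In the Data analysis section, include diagnosis, and any other factor actually stratified on, in the arm comparisons alongside arm and time.

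The cost is a wording change and one extra model term for diagnosis, given that stratified blocks are already the named procedure. The Trial status section reports that recruitment has begun, so the corrected text should be checked against the sequence in use and describe it as it is.
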